#### Secondary variables

The secondary variables (number of cannulation attempts, the proportion of correct intraventricular positioning of the perforated part of the catheter and the complication rate/adverse events) will be reported descriptively based on an intention-to-treat as well as the per-protocol population. The proportion of “early-shunt-failures” as being a safety-parameter will be reported according to the as-treated population.

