### Interventions

The procedure of cerebrospinal fluid shunting in hydrocephalus patients is an accepted neurosurgical standard. The placement of a ventricular catheter is a surgical skill that is taught early within neurosurgical training. Therefore, every neurosurgeon and neurosurgical resident is applicable to undertake the procedure within the trial as long as the handling of the catheter guide was taught within a standardised training.

The surgical technique is standardised as follows. The preparation of the skin flap is performed in order to expose at least 2 cm in diameter of the precoronal paramedian skull surface. One bore hole trepanation is performed at a localisation of 10 to 12.5 cm measured from nasion and 2 to 3.5 cm measured from midline in accordance to the individualised software measurements. The dura mater is to be coagulated and opened in order to enable the catheter puncture without being deviated at the dura level. The brain surface is punctiformly coagulated to open the leptomeningeal layers.

In treatment arm 1, the catheter guide is used with the individual parameters of coronal angulation to the skull surface and catheter length measured in a coronal section of the cranium with the catheter guide application software.

In treatment arm 2, the catheter placement is undertaken in freehand technique.

In both arms, the catheter is fixed by a rectangular redirector of the catheter from the bore hole to the subcutaneous tissue, such as a bore hole reservoir or a 90° connector.

In case of an unsuccessful cannulation, the surgeon will re-try the puncture in the freehand group. In the guided catheter group, the surgeon will repeat the use of the guide in case any mistakes in its application are detected and may need to be corrected, otherwise a crossover to the freehand technique will be performed.

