### Statistical analysis

#### Primary variable

The proportion of patients with a primary placement of grade I or Ib position of the catheter in the ipsilateral ventricle, as well as associated 95% confidence intervals, will be reported for each treatment arm. The study null hypothesis, which is to reject, states that the catheter guided treatment arm is equal or inferior to the freehand technique arm regarding the proportion of correct catheter positioning in the ipsilateral ventricle. This null hypothesis has to be disproved to state the superiority of the catheter guide treatment.

*H 0*: *P*_
*TG*
_ – *P*_FH_ < = 0 (*P*_
*TG*
_ < =*P*_
*FH*
_);

*H 1*: *P*_TG_ – *P*_
*FH*
_ > 0 (*P*_
*TG*
_ > *P*_
*FH*
_).

*P* is equal to the responder rate (TG – Thomale Guide, FH – freehand)

The analysis will be based on the intention-to-treat population in order to include catheter guide treatment problems with a change in the intraoperative treatment of the patient (cross-over). In the case of non-applicability of the catheter guide (for example, uneven bony surface) in patients randomised into the catheter guide treatment arm, they will be treated according to the freehand technique treatment arm. This is also applicable for patients with unsuccessful cannulation of the ventricle in the catheter guide treatment arm according to the decision of the operating surgeon. In the intention-to-treat analysis, all these cross-over patients will be analysed in the catheter guide treatment arm.

In a secondary step, a per-protocol reporting will be done, which excludes cross-over patients.

In a tertiary analysis as-treated reporting (safety evaluation) is foreseen.

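### Early shunt failure is reported only as-treated, although cross-over runs only from guide to freehand and can follow a failed guided pass; a report by randomised arm should be the main one

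*Protocol article*

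**What the plan says.** The article lists early shunt failure under Secondary endpoints. Secondary variables splits these endpoints by analysis set. Cannulation attempts, correct intraventricular position of the perforated part, and complications "will be reported descriptively based on an intention-to-treat as well as the per-protocol population". The proportion of early shunt failures, by contrast, "as being a safety-parameter will be reported according to the as-treated population".

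The cross-over rules are in two places. Under Interventions, a freehand patient with an unsuccessful cannulation is re-tried freehand. In the guided group the guide is used again if a mistake in its application is found; "otherwise a crossover to the freehand technique will be performed". Primary variable says that patients in whom the guide cannot be applied are treated as in the freehand arm, and adds: "This is also applicable for patients with unsuccessful cannulation of the ventricle in the catheter guide treatment arm".

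Primary variable also describes the three sets. For intention-to-treat: "In the intention-to-treat analysis, all these cross-over patients will be analysed in the catheter guide treatment arm". For per-protocol: "In a secondary step, a per-protocol reporting will be done, which excludes cross-over patients". For as-treated: "In a tertiary analysis as-treated reporting (safety evaluation) is foreseen". The article does not say where the as-treated set places a patient who had both a guided and a freehand pass.

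**The concern.** As-treated safety reporting is common and often harmless. Two features of this trial make it a poor sole choice. Patients can move in one direction only, and one of the reasons for moving is that the guide itself did not work. Moving those patients to the comparator is therefore informative. It takes out of the guide group patients who may have harder anatomy or more punctures, and adds them to the freehand group.

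Early shunt failure is also the only listed secondary endpoint for which no comparison by randomised arm is named. For the primary endpoint the article chooses intention-to-treat so that problems with the guide that lead to a change of technique are included. The same reason applies to shunt failure, where the article names only the set that can leave those problems out. At stake is a descriptive safety comparison that readers will use when judging the guide for routine use.

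**Working it through.** **Inputs from the article.** Sample size gives 65 per arm and, with 10% dropout, 72. Reproduced: 65 × 1.10 = 71.5, rounded up to 72. This is the only plan figure that the check uses. The article gives no early-failure rate and no cross-over rate. The 5% non-responder rate under Sample size is not defined as a cross-over rate; 5% is used below only as an illustrative value.

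**Assumptions.** n = 72 per arm. A share c of the guide arm crosses over. Failure risk is b in cross-overs and a in all other patients of both arms. As-treated counts cross-overs as freehand.

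**Formulas.**
- Randomised arm: guide = (1 − c)a + cb; freehand = a; difference = c(b − a).
- As-treated: guide = a; freehand = (na + ncb)/(n + nc) = (a + cb)/(1 + c); difference = −c(b − a)/(1 + c).
- Per-protocol: a in both groups; difference = 0.

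Under these assumptions the first two differences always have opposite signs unless b = a, when both are zero. If b < a, the as-treated bias goes against the guide.

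**Main illustration, a = 10%, b = 30%.**
- c = 5% (3.6 patients). Randomised: 0.95 × 0.10 + 0.05 × 0.30 = 11.0% guide, 10.0% freehand. As-treated: 10.0% guide, (7.2 + 1.08)/75.6 = 11.0% freehand.
- c = 15% (10.8 patients). Randomised: 0.85 × 0.10 + 0.15 × 0.30 = 13.0% guide, 10.0% freehand. As-treated: 10.0% guide, (7.2 + 3.24)/82.8 = 12.6% freehand.

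**Range, whole numbers of cross-overs, 5% base risk.**

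| Cross-overs of 72 | Risk in cross-overs | Randomised difference | As-treated difference |
|---|---|---|---|
| 4 | 10% | +0.3 points | −0.3 points |
| 4 | 25% | +1.1 | −1.1 |
| 7 | 25% | +1.9 | −1.8 |
| 11 | 50% | +6.9 | −6.0 |

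With a base risk of 10% and 10% in cross-overs, every difference is 0.

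**In events.** At c = 5%, excess events among cross-overs = 3.6 × (0.30 − 0.10) = 0.72. The standard error of a difference at 10% risk and 72 per arm is √(2 × 0.10 × 0.90/72) = 5.0 points.

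**If technique has no effect at all.** Suppose 5% of both arms have difficult anatomy and a 30% risk, all others have 10%, and exactly the difficult guide patients cross over. By randomised arm both groups are at 11.0%, difference 0. As-treated gives guide 10.0% and freehand (72 × 0.11 + 3.6 × 0.30)/75.6 = 9.00/75.6 = 11.9%, an apparent advantage of 1.9 points for the guide. So the bias does not require the failed guided pass to have caused harm.

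**The case against.** **The classification is inferred.** The article nowhere says that as-treated counts a patient exposed to both techniques as freehand. The sentence on treating cross-overs as in the freehand arm describes treatment, not an analysis set, and the full definitions may be in a document not shown. This stands as a limit on certainty. It does not remove the point: as-treated is the only set stated for this endpoint, and the cross-over text makes the freehand label the natural one.

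**As-treated has a rationale here.** Follow-up ties this outcome to catheter dysfunction needing re-operation, and in a cross-over patient the implanted catheter was placed freehand. Some cross-overs, such as those with an uneven bone surface, may never have had a guided pass. Both arguments support keeping an as-treated table. Neither supports having no randomised comparison.

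**The effect may be negligible.** The risks are assumed, and the Discussion reports primary cannulation for all pilot catheters, so cross-over after a failed pass may be rare. At 5% cross-over the shift is well inside sampling error. This stands and limits the severity.

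**Complications.** A reader might infer that the randomised comparison is also lost for adverse events, or that the two analysis sections contradict each other. The documents do not support either. Complications are reported by intention-to-treat, which keeps cross-overs in the guide arm; the per-protocol table is additional. A tertiary as-treated safety report can coexist with both. Nor does per-protocol remove exactly the patients with most passes, since those with repeated guided attempts and no cross-over stay in.

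**Conclusion.** The point holds for early shunt failure. As written, this endpoint has no stated comparison by randomised arm, and the one set named for it can charge failures of guided attempts to freehand. The bias favours the guide only if cross-over patients fail more often than others, which is plausible after failed passes but not quantified in the article. In the illustrations at about 5% cross-over it is roughly 1 point in each arm when the cross-over risk is 20 points above the rest, and it is zero with equal risks. It grows with the cross-over rate: from +6.9 to −6.0 points in the most extreme case shown.

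An unconditional claim that the plan shifts the guide's harm to freehand would go too far, because the direction depends on the risk in cross-overs and the classification is a reading of the text. For complications the only matter is which table leads. The confirmatory test concerns catheter position and is analysed by intention-to-treat, so it is untouched. Minor to moderate.

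**What to change.** 1. In Secondary variables, name the intention-to-treat population as the main set for early shunt failure and keep as-treated as supportive.
2. Define as-treated for patients exposed to both techniques: any patient with a guided pass is counted under the guide or shown as a separate row; a patient who crossed over before any guided pass is counted as freehand.
3. State that the intention-to-treat table is the main one for complications and that the per-protocol table is supportive only.

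The cost is wording and one extra table. Cross-overs must be identified anyway to build the per-protocol set, and Follow-up already lists the number of attempts. The sponsor should confirm that the case report form shows whether a guided pass preceded the cross-over; if not, one item is needed. The guide's safety figures may look slightly less favourable. The sample size and the primary analysis do not change.

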#### Level of significance

The one-sided test level for the confirmatory test is 2.5%. The explorative tests will be performed on a two-sided level of 5%. To adjust for multiple effects and covariates without running multiple tests, appropriate multivariate regression models will be used for analysis.

### Trial organisation

The trial is initiated and designed by the investigators. It is funded by B. Braun Aesculap. The study is conducted in 10 German medical centres (see the list at the end of this paper). These study centres were chosen for their experience in treatment of hydrocephalic patients and their willingness to adhere to the study protocol.

### Data management and monitoring

The clinical data will be reported on an electronic case report form (online) by the investigators at the study site. The access to the web-based database is individualised and password protected. The study shall be conducted according to the ISO 14155 guideline for medical device studies. Study monitoring is performed by an authorised and qualified representative of the study administration.

### Ethical aspects

The trial is approved by the ethics committee of the Charité - Universitätsmedizin Berlin. Secondary approvals are obtained from the ethics committee of each study centre. The trial is conducted in agreement with the principles of the Declaration of Helsinki and the German law for medical devices. Patients are enrolled into the trial only after a signed informed consent is obtained.

## Discussion

The placement of ventricular catheters is a relatively easy and straight-forward procedure, for which the neurosurgeons are trained during their first years of residency [1]. It may be the most often performed procedure in neurosurgery, since it becomes necessary in patients with cerebrospinal fluid drainage blockage, as transient external drainage before larger tumor surgeries, for intracranial pressure monitoring, for example, in severe traumatic brain injury patients, and in hydrocephalus patients for cerebrospinal fluid (CSF) shunting [3,5]. In all of these indications the accuracy of the ventricular catheter placement will correlate with the proper functioning of the catheter [2,6]. In the shunted hydrocephalus patients the catheter is part of a lifelong implant, thus, accurate care must be delivered for proper placement and long-term functioning of the implant [2]. This is regularly performed in freehand technique according to standardised anatomical landmarks. Recent studies have shown that this technique results in a 12.5% to 40% inaccuracy of catheter placement [2,4,8,9]. Thus, in selected cases, technical efforts, such as neuronavigation and ultrasound, were used to enhance the proportion of accuracy [3,7,11,12,16]. The reason for not using it in all cases is that the preparation time of technical advances is too long in relation to the procedure itself and the availability in each centre for these procedures are limited [12]. Another aspect is a limited awareness of neurosurgeons concerning the failure rate of accurate positioning of the catheter in a rather simple procedure. This holds especially true since the failure of a catheter which is inaccurately placed will happen within an interval when the correlation to the initial procedure cannot be drawn anymore. A survey among neurosurgeons about the use of technical efforts for the accurate placement of ventricular catheter disclosed that 30% did not want to enhance the freehand method while roughly 60% would use technical advances if they would not prolong the surgery by 5 or 10 minutes [10]. With these conditions, we recently introduced a mechanical instrument for guiding ventricular catheter placement. For this technique, one individual parameter is necessary to be measured in preoperative imaging and applied to this instrument to achieve controlled and accurate puncture of the ventricle via a frontal pre-coronal approach. The safety and efficacy of this technique was shown in a single centre study so far [14]. The proposed protocol is designed to prospectively test the method on the larger basis of a multicentre randomised trial.

Our own retrospective analysis of inaccurate placement of the ventricular catheter reveals that the inaccuracy correlates with smaller ventricles. We found that an FOHR of smaller than 0.5 resulted in 15% catheter malpositioning at our institution. This cutoff measure represents a ventricular size in which regularly no technical help is applied for better accuracy. The catheter guide is thus meant to be used in a routine manner even if the ventricular size seems not necessarily to be challenging, but to achieve a higher level of reliability of the lifelong implanted ventricular catheter.

The technique itself incorporates innovatively the good availability of smartphones as a measurement tool for the surgical instrument. Hereby, an application software was designed in order to easily apply the measurements in one coronal brain section image. Virtual visualisation of the instrument does help to perform the measurements intuitively and to safely apply the measures to the instrument and the patient.

The image processing can also be done on every advanced DICOM viewer, which allows in-picture-angle-measurements. However, we experienced herewith a more complicated workflow and a higher risk that the measurements are not accurately transferred to the patient. The images used for the smartphone application must be coronal sections where the frontal horns are depicted [14]. Herein, the trajectory will be projected from oblique to strictly coronal. This can be transferred as an anonymous image file, for example, via e-mail to the smartphone and may then be integrated in the software application. When higher accuracy is needed, the image section can also be reconstructed along the virtual trajectory of the catheter placement using a navigation-software. This will enable the measurements to be done at the exact localisation of the entry point. In more difficult cases, such as slit ventricles (FOHWR <0.05), a neuronavigation system for ventricular catheter positioning might still be advantageous.

According to our initial data, the catheter guide used in combination with the iPhone application revealed a good reliability in the pilot study. Here, the catheter guide was used in narrow ventricles with a mean FOHR of 0.38+/−0.05. All catheters could be placed in a functional correct position with primary cannulation. In 8%, the contralateral ventricle was punctured, which was observed within the first 10 patients, so a learning curve in using the catheter guide must be stated [14].

The catheter guide has to be used directly on the bony surface to ensure the angulation be applied in relation to the surface of the skull. That may limit the use of the catheter guide when insufficient bone area is exposed or the surface may be uneven due to previous surgeries at the site of the entry point. Transcutaneous cannulation of the ventricles, for example, in the case of an external ventricle drainage as performed on intensive care units, are not applicable with the current design of the tool.

The placement of ventricular catheters is a frequent procedure in Neurosurgery which is regularly performed in freehand technique. As recent literature has reported this is not sufficient for lifelong implants as ventricular catheters are used in CSF shunts for hydrocephalus patients. An easy to use surgical instrument used together with a smartphone software application is tested within the current study design in a prospective randomised multicentre fashion in order to evaluate its safety and efficacy for the routine use in a wide range of patients.

### Current status

A first investigators’ meeting was held in May 2012, where the key points of the study design were discussed and agreed on by all clinical trial centres. In November 2012, the study protocol was then completed and the trial was approved by the ethics committee of the Charité - Universitätsmedizin Berlin on 18 February 2013. On 8 April 2013 the first patient was enrolled in the GAVCA trial. The estimated patient recruitment time for 144 patients in 10 study centres is 24 months. At the time of submission, 24 patients were recruited in 5 out of 10 participating centres.

## Abbreviations

CSF: Cerebrospinal fluid; GAVCA: Guided Application of Ventricular Catheters; FOHR: Frontal occipital horn ratio; FOHWR: Frontal occipital width ratio; VC: Ventricular catheters.
